### Post study data collection

The weight gain charts will be retrieved from the pregnancy notes after women have had their baby. We do not expect to have sufficient power within this trial to detect statistically significant differences in maternal and neonatal complications but these data will be obtained from medical records at each hospital and described in the trial reports to contribute to future meta analyses. The following information on pregnancy will be collected mode of delivery, inpatient days for the mother, maternal ICU admission, preeclampsia, pregnancy induced hypertension, gestational diabetes, maternal sepsis, preterm delivery, miscarriage, stillbirth, shoulder dystocia, treatment for jaundice, admission to the neonatal intensive care unit (duration of stay if relevant and inpatient days), neonatal death and 1 and 5 min Apgar score and neonatal sepsis. Data on infant birth weight and gestational age at delivery will also be collected from hospital electronic records.

### Adverse and serious adverse events requiring hospitalisation

There are several reasons to believe the intervention is safe and will not cause adverse events. We are not testing a dangerous intervention; the treatment consists of regular weighing and feedback as part of routine antenatal care, along with self monitoring of weight at home, none of which seem likely to create harm. Therefore, we will not monitor the occurrence of all adverse events by trial group as it will be burdensome for midwives and participants. We will only report unexpected serious adverse events and deaths to the research ethics committee. Expected serious adverse events (that will not be reported to the ethics committee) are defined as preeclampsia, gestational diabetes, stillbirth, neonatal death, termination due to abnormality, gestational hypertension, cerebrovascular accident, myocardial infarction, pre term delivery, termination, miscarriage, severe mental health illness, antepartum haemorrhage, thromboembolism, maternal sepsis, maternal admission to intensive care, hysterectomy, visceral injury, neonatal admission to the special care baby unit, neonatal infection, neonatal respiratory distress.

### Sample size

A total of 610 (305 per group) is sufficient to detect a 15 percentage points difference (45 % versus 60 %) [4–7, 39] in the proportion who, at 38 weeks of pregnancy, exceed the IOM guideline for gestational weight gain according to their baseline pregnancy BMI in the intervention group compared to usual care (90 % power, 5 % significance level). Previous prevention trials [31, 41], have reported between 10–25 % points difference between the proportion in intervention and control groups that exceed the IOM cut-offs for gestational weight gain, depending on intervention intensity and the population, we have been cautious in expecting 15 % points difference. The sample size includes allowance for 20 % loss to follow up at 38 weeks of pregnancy. 610 participants would also be sufficient to detect 1.6 kg difference in mean weight at 38 weeks of pregnancy (SD weight change of 5.5 kg from our pilot RCT [50], 90 % power, 5 % significance level).

### Statistical analysis

Baseline characteristics including age, social class, ethnicity and parity will be presented by randomisation group using summary statistics. The primary analysis will focus on the proportion of women who exceed the IOM guidelines for gestational weight gain at ~38 weeks of pregnancy (primary outcome). The difference in these proportions between the groups (and odds ratio) will be calculated along with associated confidence interval using mixed effects logistic regression modelling. The analysis will adjust for BMI category (healthy weight, overweight, obese) and site (Birmingham, Dudley, Oxford, Warwick) as fixed effects and midwife as a random effect. Missing weight data for births occurring after 37 weeks (excluding pregnancy loss), will be imputed using multiple imputation. Linear mixed modelling will be used to compare the secondary outcomes of weight gain per weeks of pregnancy, depression, anxiety, physical activity and diet recorded at ~38 weeks of pregnancy. Mother and baby pregnancy complication rates will be summarised by group. In a planned but exploratory subgroup analysis, BMI categories (healthy weight, overweight, obese) will be compared for the primary outcome by its inclusion as an interaction term (intervention by BMI category) in the modelling. There are no other planned subgroup analyses. A sensitivity analysis of the primary outcome will be performed without imputing missing weights. Treatment effects, 95 % confidence intervals, and two-sided p values will be reported for all comparisons. Analyses will be undertaken using an intention to treat approach. Full details of analysis will be pre-specified in a separate statistical analysis plan.

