### Outcome measures

The primary outcome is the proportion of participants per group who exceed the IOM guidelines for gestational weight gain according to their early pregnancy BMI category from baseline to 38 weeks of pregnancy. Secondary outcomes are the difference in weight gain per weeks of pregnancy between the groups**,** difference in total weight from baseline to 38 weeks of pregnancy between the groups and difference in changes in psychological health, physical activity and diet quality between the groups from baseline to 38 weeks of pregnancy.

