### Randomisation and blinding

The telephone randomisation service at the Primary Care Clinical Research Trials Unit (PCCRTU) will be used to randomly allocate participants to trial groups. The randomisation list will be developed by a statistician within the Trials Unit using NQuery Advisor. Participants will be individually randomised to usual care plus intervention or usual care only on a 1:1 basis using random permuted blocks of random size. The list will be stratified by BMI category at recruitment (healthy weight, overweight, obese) and maternity site (Birmingham, Oxford, Dudley & Warwick). The primary outcome is measured by community midwives at routine 38 week pregnancy appointments, therefore they will not be blinded to group allocation but we have no reason to believe midwives will not record these data accurately. The trial statistician will remain blinded to group allocation until analysis is completed.

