### Descriptive data

Data will be collected about participants’ demographic details, smoking status and weight management history at recruitment.

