### Baseline assessment

All trial women will be weighed by the research team using calibrated scales and have their height measured with excess clothing (i.e. shoes and coats) removed. The study baseline questionnaires will also be completed measuring anxiety and depression, physical activity and diet quality.

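### The primary logistic model is valid and adequately powered at its target, but it leaves unused some recorded baseline variables, such as gestation and continuous BMI at recruitment, that could add a little power at almost no cost

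*Protocol article*

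**What the plan says.** The Statistical analysis section of the protocol article fixes the covariates of the primary mixed-effects logistic model: "The analysis will adjust for BMI category (healthy weight, overweight, obese) and site (Birmingham, Dudley, Oxford, Warwick) as fixed effects", with the sentence ending "as fixed effects and midwife as a random effect". The results are to be a difference in proportions and an odds ratio, each with a confidence interval. The two fixed effects are the randomisation strata. Under Randomisation and blinding: "The list will be stratified by BMI category at recruitment (healthy weight, overweight, obese) and maternity site".

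Other baseline information is recorded but given no role in this model:

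- Baseline assessment: "All trial women will be weighed by the research team using calibrated scales and have their height measured". BMI is therefore measured on a continuous scale, although it enters the model as three bands.
- Descriptive data: demographic details are collected, with "smoking status and weight management history at recruitment".
- Statistical analysis: "Baseline characteristics including age, social class, ethnicity and parity will be presented by randomisation group using summary statistics".
- Gestation at recruitment is an eligibility criterion (10+0 to 14+6 weeks), so it is known for every woman.

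Outcome measures defines the primary outcome as exceeding the Institute of Medicine limit "according to their early pregnancy BMI category from baseline to 38 weeks of pregnancy". Further analysis detail is left to a separate SAP, which is not shown.

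**The concern.** Adjusting for baseline variables that predict the outcome generally raises the power of a randomised comparison, and it removes chance imbalance in those variables. The covariates here are a stated choice rather than an open detail, and variables that might help are already in the database.

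Gestation at recruitment has a claim that comes from the document itself. If gain is counted from baseline to 38 weeks, a woman recruited at 10+0 has almost five more weeks of counted gain than one recruited at 14+6, against a limit fixed by BMI category. The stratification does not control gestation, parity or smoking, and it balances BMI between bands but not within them.

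At stake is a modest amount of efficiency in the one primary test. The validity of that test is not in question.

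**Working it through.** **1. Reproduce the planned sample size.** Inputs from the second Sample size section: 45% versus 60%, 90% power, 5% significance, 20% loss. The test is two-sided (Statistical analysis).

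- Two proportions, no continuity correction: n = [1.960 × √(2 × 0.525 × 0.475) + 1.282 × √(0.45 × 0.55 + 0.60 × 0.40)]² / 0.15² = 230.8, so 231 per arm.
- With continuity correction: (230.8/4) × [1 + √(1 + 4/(230.8 × 0.15))]² = 243.98, so 244 per arm.
- Allowing for loss: 244/0.80 = 305 per arm, 610 in total. This matches the plan exactly.

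The stated 90% power therefore comes from an unadjusted comparison and relies on no covariate.

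**2. What gestation at recruitment can contribute.** The slope comes from the worked chart example (Fig. 2 caption), where the mid-line target is 63.5 kg at 16 weeks and 67 kg at the 25-week appointment. One sentence of the caption attaches the 67 kg to 16 weeks, but the target is being set for 25. The SD of weight change, 5.5 kg, is from Sample size.

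- Slope: 3.5 kg / 9 weeks = 0.389 kg/week.
- Window: 34 days = 4.857 weeks.
- End to end: 4.857 × 0.389 = 1.89 kg, and 1.89/5.5 = 0.343 SD. For a woman near the limit, Φ(0.172) − Φ(−0.172) = 0.136, about 14 percentage points.
- Variance explained, which is what governs power: with uniform recruitment over the window (assumption), the SD of gestation is 4.857/√12 = 1.40 weeks. That is 1.40 × 0.389 = 0.545 kg, and (0.545/5.5)² = 0.0098, about 1% of the variance of gain.
- Upper bound, with half the women at each end of the window: (2.429 × 0.389/5.5)² = 0.029, about 3%.

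In a simulation of a normally distributed gain cut at the limit (244 per arm, 4,000 trials), a covariate score explaining 1% of gain variance gave an information ratio of 1.005. That is worth about 0.005 × 610 = 3 women.

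**3. What a set of covariates could contribute.** R² is the share of variance in the binary outcome explained beyond the present model. The document gives no value, so the range is assumed. Effective n = 244/(1 − R²), and the risk-difference interval width scales as √(1 − R²).

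| R² (assumed) | Power at 45% v 60%, continuity-corrected | Relative interval width |
|---|---|---|
| 0 | 90.0% | 1.000 |
| 0.01 | 90.3% | 0.995 |
| 0.05 | 91.5% | 0.975 |
| 0.10 | 92.9% | 0.949 |

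**4. Check by simulation.** Logistic regression without and with one prognostic covariate, 244 per arm, 4,000 trials per row. BMI, site and midwife were not simulated.

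| R² | Power, without → with | SE of log OR | SD of risk difference |
|---|---|---|---|
| 0.015 | 92.1% → 92.2% | 0.184 → 0.186 | 0.0441 → 0.0439 |
| 0.054 | 91.0% → 92.4% | 0.184 → 0.190 | 0.0448 → 0.0437 |
| 0.107 | 91.2% → 94.0% | 0.184 → 0.196 | 0.0449 → 0.0422 |

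Each power figure has a Monte Carlo error of about √(0.92 × 0.08/4,000) = 0.4 points, so the differences between rows in the first power figure are mostly noise. The SE of the log odds ratio rises with adjustment. Power improves because the conditional log odds ratio moves further from zero (at R² 0.054, from −0.607 to −0.644).

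**The case against.** The strongest reply is that nothing here is wrong. The model adjusts for both stratification factors, allows for midwife, contradicts no other section, and delivers its stated power. Extra prognostic covariates are often settled in the SAP, and no section says that parity, smoking or BMI within band predicts exceeding the limit. All of that stands, and it is why this is an optional improvement. What remains is that the article does fix a covariate list, and the list can be improved with data already held.

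Two stronger readings are tempting, and the documents support neither.

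- A reader might infer that the trial throws away precision for no return. The standard error of the log odds ratio would rise under adjustment, the gain in power is small, and adjustment has a minor cost of its own.
- A reader might set the 14-point gestation figure beside the 15-point target effect and conclude that gestation seriously disturbs the comparison. That figure contrasts the two ends of the window for a woman at the limit, and randomisation balances gestation between arms on average. The slope is also an ideal chart line for weeks 16 to 25, not observed gain in weeks 10 to 14. Moreover, the section on weighing and charts assumes average prior gain for gestation when the chart is prepared. If the outcome were scored on that basis, much of the gestation effect would already be offset. If counting gain only from baseline is itself a problem, it concerns the outcome definition, which covariates do not repair.

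In favour of acting, the power is less comfortable below the target. At 60% versus 48% with 244 per arm it is about 76% without continuity correction, and about 76% to 80% for R² of 0.01 to 0.10.

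**Conclusion.** The point holds as a low-severity, optional gain in efficiency. The primary analysis as stated is valid and needs no rescue.

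If the added covariates explain 1% to 10% of outcome variance, the approximation and the simulation agree that power at the 15-point target rises by about 0 to 3 percentage points. The approximation puts the narrowing of the risk-difference interval at about 0.5% to 5%, and the simulation is close to that (about 6% at R² 0.107). There is no reduction in the standard error of the log odds ratio.

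Two assumptions carry these figures: the R² range, which has no source in the document, and uniform recruitment over the gestation window, which gives the figure of about 1% of gain variance for gestation alone. The upper end of the range would have to come mainly from BMI within band, parity and smoking, whose strength is unknown here.

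**What to change.** Before unblinding, state in the Statistical analysis section and in the SAP that the primary model includes gestation at recruitment (in days) and continuous BMI at recruitment as further fixed effects, alongside BMI category, site and the midwife random effect. Parity and smoking status may be added if the team expects them to be prognostic. In addition:

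- use the same covariates in the multiple imputation model;
- make the standardised difference in proportions, averaged over the covariates, the headline result, with the odds ratio beside it;
- keep the currently stated model as a sensitivity analysis.

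The cost is a sentence or two in each document and no new data. The downside is a few degrees of freedom and an odds ratio conditional on more covariates, which is why the standardised difference should lead.

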### Secondary objectives

To assess the difference in weight gain per weeks of pregnancy between the groups.To compare the difference in change in total weight gain during pregnancy between the groups.To compare the difference in changes in psychological health, physical activity and diet quality between the groups.To compare the occurrence rates of common complications of pregnancy (e.g. c-section, hypertension in pregnancy and gestational diabetes) between the groups.

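### Questionnaire outcomes are defined as changes from baseline but described in the analysis as 38-week values with no stated baseline term; total weight change is not in the analysis list, and the 1.6 kg power statement is mislabelled

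*Protocol article*

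**What the plan says.** All references are to the protocol article.

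- **Secondary objectives:** "To compare the difference in changes in psychological health, physical activity and diet quality between the groups". Change in total weight gain is a separate objective from weight gain per week.
- **Outcome measures:** the questionnaire outcomes are the "difference in changes in psychological health, physical activity and diet quality between the groups from baseline to 38 weeks of pregnancy". Total weight is the "difference in total weight from baseline to 38 weeks of pregnancy between the groups".
- **Baseline assessment:** the matching baselines are collected. "All trial women will be weighed by the research team using calibrated scales", and "The study baseline questionnaires will also be completed measuring anxiety and depression, physical activity and diet quality".
- **Statistical analysis:** "Linear mixed modelling will be used to compare the secondary outcomes of weight gain per weeks of pregnancy", followed in the same list by "depression, anxiety, physical activity and diet recorded at ~38 weeks of pregnancy". Adjustment for BMI category, site and midwife is given just before, after the primary logistic model. No baseline score is mentioned, and total weight change is not listed. Full details are left to a separate SAP.
- **Sample size (the later section of that name, before Statistical analysis):** 610 women are said to be enough to detect a 1.6 kg "difference in mean weight at 38 weeks of pregnancy" with 90% power at the 5% level. The SD used is 5.5 kg, labelled there as the SD of weight change in the pilot trial.

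**The concern.** A change from baseline and a value recorded at 38 weeks are different outcome variables with different variances. When one section defines the first and another analyses the second, either could later be presented as the planned analysis. The Discussion relies on advance declaration of outcomes as protection against selective reporting, and that protection is incomplete while both versions stand.

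The second stake is precision. A comparison of 38-week scores alone leaves chance baseline differences in the estimate and gives a wider interval than one adjusted for baseline. This matters most for HADS. The Background reports worries that regular weighing may cause anxiety. The adverse events section will not monitor all adverse events by group and counts severe mental health illness among the expected events not reported to the ethics committee. No data monitoring committee is planned. HADS is therefore the main between-group evidence on anxiety and depression, and for an outcome meant to reassure, the width of the interval decides what can be ruled out.

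Total weight change is also left without a stated analysis, although weight is the only secondary outcome with a power statement. That statement names one variable and uses the SD of another.

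**Working it through.** **1. The power statement.** Inputs from the Sample size section: 305 per group, 20% loss, difference 1.6 kg, SD 5.5 kg, α = 5% (two-sided, as Statistical analysis states), 90% power. Clustering by midwife is ignored, as the stated inputs imply.

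- Analysed per group: 305 × 0.8 = 244.
- Standard error: 5.5 × √(2/244) = 0.498 kg.
- Power: Φ(1.6/0.498 − 1.96) = Φ(1.25) = 89.5% (89.4% with the t distribution).
- Detectable difference at 90% power: (1.960 + 1.282) × 0.498 = 1.61 kg.
- Required n: 2 × (3.242 × 5.5/1.6)² gives 249 per group; 249/0.8 gives 312 per group, or 624 in total. That is 2.3% above 610.

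The stated 90% therefore reproduces when 5.5 kg is the SD of the variable analysed, that is, weight change. It does so under the label in Outcome measures, not under the label in Sample size.

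**2. The questionnaire outcomes.** Let σ² be the variance of a score, taken as equal at both times, and r the correlation between baseline and 38 weeks. The article does not give r; 0.3 to 0.7 is assumed. Variance of the treatment effect relative to a comparison of 38-week scores alone:

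- change score: 2(1 − r)
- 38-week score adjusted for baseline: 1 − r²

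Detectable difference at 90% power, assuming 244 per group also return questionnaires: 3.242 × √(2/244) = 0.293 SD for 38-week scores alone, multiplied by √(1 − r²) with adjustment.

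| Assumed r | Change score | Baseline-adjusted | Detectable difference, adjusted (SD) |
|---|---|---|---|
| 0.3 | 1.40 | 0.91 | 0.280 |
| 0.5 | 1.00 | 0.75 | 0.254 |
| 0.7 | 0.60 | 0.51 | 0.210 |

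The two candidate analyses do not rank the same way throughout: the change score is less precise than the 38-week score below r = 0.5 and more precise above it. The adjusted analysis is at least as precise as either. Under randomisation all three have the same expected treatment effect, so the choice affects precision and pre-specification and does not introduce bias.

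**3. Outcomes set against analyses.** Weight gain per week is defined and analysed, and it already uses baseline weight. Total weight change is defined, and the power statement concerns it, but it is not named in the analysis. Psychological health, activity and diet are defined as changes and described in the analysis by their 38-week values.

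**The case against.** The strongest reply is that nothing in the article says the baseline is left out. Statistical analysis gives the secondary outcomes one sentence. The covariates named there follow the primary model, whose binary outcome has no baseline score. Details go to an SAP that is not shown. The reference to 38 weeks may only give the follow-up time, since the same list opens with weight gain per week, which cannot be computed without baseline weight. This stands as far as it goes. A reader might infer that the trial will discard the baseline questionnaires, but the article is silent on that and does not plan it. What the reply does not remove is the conflict in wording: the outcome is a change in two sections and a 38-week value in a third. An SAP would have to depart from one of them.

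A reader might also infer that the weight comparison is badly underpowered. If raw 38-week weight were compared without baseline, an assumed SD of 10 to 15 kg would give 42% to 22% power for 1.6 kg with 244 per group. No section plans that analysis, the article gives no SD for 38-week weight, and the 5.5 kg is openly labelled as the SD of change. The figure is right and its label is wrong.

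It is also fair to say that an analysis of 38-week scores alone would be unbiased, and that its interval would already allow for chance imbalance.

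**Conclusion.** The point holds as a minor inconsistency. Three things need reconciling: change against 38-week value for the questionnaire outcomes, total weight change missing from the analysis list, and 38-week weight paired with the SD of weight change.

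The precision at stake for the questionnaires is a variance reduction of 9% to 49% for r of 0.3 to 0.7. That range rests on two conditions: an assumed correlation, and an eventual analysis of 38-week scores without baseline. The article leaves that analysis open but does not establish it. For weight, the stated power and N = 610 do not change once the endpoint is named correctly. The primary outcome is unaffected.

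**What to change.** 1. In Statistical analysis, state that each 38-week questionnaire score is compared between groups in the planned linear mixed model with its baseline score as a covariate, alongside BMI category, site and midwife. This estimates the same contrast as the objective about changes.
2. Add total weight change from baseline to 38 weeks to the analysed outcomes, adjusted for baseline weight. Gestation at the final weighing should not be added as a covariate without a justification: Follow up allows catch-up weighing after 38 weeks, so it is a post-randomisation variable.
3. In Sample size, describe the 1.6 kg as a difference in mean weight change from baseline to 38 weeks.

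The cost is a few sentences and one covariate per model. The baseline data are already collected and no sample size changes. The only addition needed is a simple rule for missing baseline scores.
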